### Sample size {14}

The number of villages for the cRCT is estimated at 17 per treatment arm based on the power analysis which is detailed in the Statistical Analysis Plan.

The sample size determination on the required number of households per cluster for testing the primary hypothesis on PE is based on the hazard rate comparison in the proportional hazards regression model. With the following specifications: power = 80%, 2-sided type-I error rate = 5%.True PE/Minimum effect size = 35%Baseline first-time malaria infection hazard rate = 1.5 cases of falciparum malaria per person-year (conservative estimate based on control arm data from first SET cRCT)Coefficient of variation (k) = 40% (based on first SET cRCT)Loss to follow-up (LTFU) rate = 20%Monitoring = 2 years to capture 2 peak transmission seasonsOne interim analysis for efficacy and non-binding futility with the O’Brien-Fleming error spending function when 50% information is collected

With 17 clusters per treatment, 55 children (aged 0.5 to 10 years old) from 55 different households per cluster are expected to yield 1315 independent first-time malaria events with a 24-month follow-up period to yield 80% power in testing the primary hypothesis on PE. Since the sample size already factors in a 20% LTFU rate, there is no need for replacement subjects.

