##### Primary

Protective efficacy (PE) against clinical malaria infection will be determined by comparing hazard rates of malaria clinical cases between the two treatment arms based on an intention to treat (ITT) analysis. The primary hypothesis on PE against overall malaria case incidence will be tested by comparing the hazard rates of the overall malaria case incidence between the control and ET in the ITT population using a proportional hazards model. The model will include relevant individual-level, household-level, and cluster-level baseline covariates, treatment assignment, and follow-up visits and random effects to account for correlations among the subjects within the same cluster and among multiple infections within the same individual. The hazard ratio $$\beta$$ between ET and control will be estimated, along with a 95% confidence interval. The null hypothesis of PE = 0% is equivalent to $$\beta =0$$, which will be tested by the Wald’s test $$z=\widehat{\beta }/s$$, where $$s$$ is the estimated standard error of $$\widehat{\beta }$$. There will be one formal interim analysis to test the primary hypothesis. The decision boundaries are calculated for either stopping for futility or stop for efficacy using the O’Brien-Fleming error spending function [8–10], with a 2-sided Type I error rate of 0.05, Type-II error rate of 0.2; baseline incidence rate of 1.5 per person-year, and between-cluster CV of 40%. The interim analysis will occur when 658 events (50% information) are collected. Assuming a baseline incidence rate of 1.5 per person-year, the interim analysis is estimated to occur around the end of Year 1 of the intervention follow-up. Due to the formal interim look at the data which costs a certain amount of type-I error rate and type-II error rates, the final critical value is different from what would be for a study without the interim look.

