If the z-score of the log(hazard ratio) from the comparison between ETs and control at the interim look is >  − 0.7288 then the study can stop for futility (if *z*-score > 2.7965, the trial would stop for definitive harmful effects of ETs though the chance this would occur is close to 0 if not 0), the study can stop for futility. Since we adopt the non-binding futility boundary the study can continue to collect more data even if we cross the futility boundary at the interim look, there will be no inflation of type I error. In other words, the trial does not need to stop to accept the null hypothesis when the test statistic falls in the futility region at the interim stage. If the interim z-score <  − 2.7965 then the study can stop for efficacy. The study may also continue even if the efficacy boundary is crossed at the interim look, and there will be no inflation of type I error as efficacy is already established at the interim. If the interim z-score falls within (− 2.7965, − 0.7288), the study continues.

If the interim results do not cross either the futility or efficacy boundaries, the *z*-score from the final analysis upon the completion of the study will be compared with − 1.9744. If the *z*-score <  − 1.9744, we reject the null hypothesis, claiming ETs reduce the malaria hazard rate compared to control at the significance level of 5%; if the *z*-score > 1.9744, we fail to reject the null hypothesis, claiming ETs do not reduce the malaria hazard rate compared to control in Cote d’Ivoire. If the interim results cross either the futility or efficacy boundaries, the final analysis is only conducted for estimation purposes, as the futility or efficacy of ETs is already established at the interim.

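### The primary Wald test uses a normal cut-off at a claimed 5% level although the effect rests on 17+17 villages, and the printed boundary pair does not fit the stated 50% information

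*Protocol article*

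**What the plan says.** In the protocol article, Statistical methods, Primary, the null hypothesis of no protective efficacy is one "which will be tested by the Wald’s test", with z equal to the estimated log hazard ratio over its standard error. The estimate comes from a proportional hazards model with random effects for village and child and with baseline covariates at individual, household and village level.

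The bounds are for "stopping for futility or stop for efficacy using the O’Brien-Fleming error spending function". The design values behind them are a two-sided error of 5%, power of 80%, 1.5 control events per person-year and a coefficient of variation between villages of 40%. Timing is fixed too: "The interim analysis will occur when 658 events (50% information) are collected". Sample size {14} agrees, planning one interim look with the O'Brien-Fleming "error spending function when 50% information is collected", and 55 children in each of 17 villages per arm, who "are expected to yield 1315 independent first-time malaria events with a 24-month follow-up period".

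The Primary section then prints the numbers: efficacy at the interim below −2.7965, non-binding futility above −0.7288, and a final comparison with −1.9744. Crossing the final value is read as "claiming ETs reduce the malaria hazard rate compared to control at the significance level of 5"%. The text as shown mentions no t reference and no small-sample correction.

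**The concern.** The plan names a method, an information fraction, a pair of bounds and an error level. The four should agree, and they do not.

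Separately, fixed normal-theory cut-offs suit a statistic whose standard error is practically known. Here the standard error is estimated mainly from the spread among 34 villages. A statistic of that kind has heavier tails than a normal one, so a normal cut-off rejects too often. This test decides the primary hypothesis in a trial meant for the WHO advisory group's assessment of public health value, and a borderline result could be called significant at a level that the plan does not deliver.

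**Working it through.** **1. The boundary pair.** Inputs from the Primary and Sample size sections: two-sided 0.05, one interim look, information fraction 0.5 (658/1315 = 0.5004), printed pair 2.7965 / 1.9744. The interim and final z are taken as bivariate normal with correlation √t.

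- O'Brien-Fleming spending function, 0.025 per side, t = 0.5: the amount spent per side is 2[1 − Φ(2.2414/√0.5)] = 0.00153. The interim bound is 2.9626 and the final bound, solved numerically, is 1.9686.
- Classical two-look O'Brien-Fleming, t = 0.5: solving P(|Z1| > c√2 or |Z2| > c) = 0.05 gives c = 1.9774 and c√2 = 2.7965.
- Spending function solved for the fraction at which the interim bound is 2.7965: t = 0.5532, final bound 1.97437, overall error 0.0500. This reproduces both printed values. It corresponds to 0.5532 × 1315 ≈ 728 events, not 658.
- Overall two-sided error of the printed pair at t = 0.5: 0.0503.

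**2. How much of the variance lies between villages.** Inputs: CV 0.40, control rate 1.5 per person-year, 55 children per village, 20% loss. Taking 55 × 0.8 = 44 person-years per village-year gives 66 control events per village in one year and 132 in two. The approximate variance of a village log rate is CV² + 1/events.

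- Two years: 0.16 + 1/132 = 0.1676, of which 0.16/0.1676 = 95% is between villages.
- So the standard error is essentially a between-village estimate, with about 34 − 2 = 32 degrees of freedom. Each village-level covariate removes one more.

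**3. Error of the normal cut-off, unbiased variance.**

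- P(|t32| > 1.9744) = 5.70%.
- The article names two village-level baseline characteristics (population and baseline prevalence). With both in the model, P(|t30| > 1.9744) = 5.76%.

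**4. Error if the village variance is a maximum-likelihood estimate** (an assumption). Such an estimate divides by 34 instead of 32 − k, so the effective cut-off is 1.9744 × √((32 − k)/34) on 32 − k degrees of freedom, for k village-level covariates.

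- k = 0: 1.9744 × √(32/34) = 1.915, and P(|t32| > 1.915) = 6.4%.
- k = 1, 2, 3: 6.9%, 7.4%, 7.9%.

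Simulation without a treatment effect agrees. These models used constant-hazard Poisson counts with a village random effect, fitted by maximum likelihood, as a stand-in for the planned frailty model.

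- One set gave 6.4% with no covariates (3,885 trials) and 7.6% with three (1,807 trials).
- Another (6,000 trials per setting) gave 6.1% and 7.5% with 0 and 2 covariates under gamma frailty, and 7.6% and 8.2% under log-normal frailty.
- With four covariates that second set gave 8.4% and 9.6%.
- Using 1.9774 instead of 1.9744 moved these results by at most 0.1 point, so correcting the pair does not cure the inflation.

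**5. Confidence intervals.** A normal multiplier of 1.960 against t32 = 2.037 makes the interval about 4% too narrow (2.037/1.960 = 1.039). With the maximum-likelihood factor √(34/32) = 1.031 the ratio is 1.071, about 7%.

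**6. Events are not information here.** Information in this Wald statistic is the inverse of its variance. After one year the village variance is 0.16 + 1/66 = 0.1752, so the fraction is 0.1676/0.1752 = 0.96. This matches the correlation of about 0.98 between interim and final z in the simulation (0.98² = 0.96).

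**The case against.** The strongest reply on the boundaries is that the named method does reproduce both printed values, at an information fraction of 0.553. That stands. A reader might infer that the pair belongs to no O'Brien-Fleming version, or that 1.9744 is a digit slip for 1.9774. The documents do not support either reading. Because 2.7965 is also the classical value at 50%, the origin cannot be settled from the article. What remains is the conflict with the stated 50%, worth 0.03 points of error.

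A second reply is that, with interim and final z as closely correlated as step 6 implies, the printed pair would give 4.8% if z were truly normal. That also stands: the extra look is not what inflates the error.

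Third, a reader might take 6–8% as the test's actual error rate. The article gives neither the estimator nor the frailty shape nor the final covariate list, and the simulations omit the child-level random effect. Baseline prevalence may also absorb part of the village variance. The range is therefore conditional. The 5.7% does not depend on the estimator. Nor would informative covariates remove the problem easily: if they halved the village variance to 0.08, its share would still be 0.08/(0.08 + 1/132) = 91%.

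Finally, a Wald z is conventional, and small-sample corrections are usually left to the SAP, which is not shown. But the article itself prints the statistic, the four-decimal cut-off and the 5% claim. If the SAP contains a correction, the article's fixed z cut-off conflicts with it.

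**Conclusion.** The concern holds in two parts of very different weight.

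- **Boundary pair:** inconsistent with the stated 50% information under the named spending function. The effect on the error rate is negligible (5.03%), but the interim stopping bound differs visibly (2.7965 against 2.963).
- **Normal reference:** anti-conservative with 17+17 villages at a CV of 40%. The two-sided error is about 5.7% with an unbiased variance and 32 degrees of freedom. It is roughly 6–8% under maximum likelihood with 0–3 village-level covariates. Intervals on the same reference are about 4% to 7% too narrow.

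The direction does not depend on the modelling choices, but the exact size does. This should be corrected before the primary analysis. It does not affect how the trial is run in the field.

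**What to change.** - Reconcile 2.7965 / 1.9744 with the stated information fraction, and say which method and fraction produced them.
- State that the bounds will be recomputed from the spending function at the fraction realised at the interim, measured by the inverse squared standard error and not by event counts alone. At the planning CV these differ greatly (0.96 against 0.50), so the definition should be settled before the interim look.
- Refer the final statistic and its confidence interval to a t distribution with degrees of freedom equal to villages minus village-level parameters, using a REML-type variance. At 32 degrees of freedom, final normal bounds of 1.9686 to 1.9774 convert to 2.046 to 2.056, about 2.05. Alternatively, take the primary p-value from a permutation test over the village allocation, following whatever stratification was used in the randomisation.
- If the SAP already has such a correction, align the article's cut-off and wording with it.

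The cost is wording, a few lines of code and about 2 points of power. As an illustration, a 35% reduction gives ln 0.65 = −0.431. The ET arm has 0.65 × 132 = 85.8 events per village, so the standard error is √[(0.16 + 1/132 + 0.16 + 1/85.8)/17] = 0.141 and the standardised effect is 3.05. Power from the noncentral t on 32 degrees of freedom, before futility stopping, falls from 85.5% at 1.9744 to 83.6% at 2.056. No new data are needed.

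### The final decision rule assigns non-rejection to the wrong side of zero, and it cancels the final test after a futility crossing although that boundary is declared non-binding

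*Protocol article*

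**What the plan says.** All the statements are in the Primary subsection of the protocol article's statistical methods {20a}. Negative z favours EaveTubes (ETs).

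- **Interim look.** "The interim analysis will occur when 658 events (50% information) are collected". A z below −2.7965 allows stopping for efficacy, and a z above −0.7288 allows stopping for futility. A z above +2.7965 is described as a stop for harm.
- **Status of futility.** The boundary is called non-binding, and "the trial does not need to stop to accept the null hypothesis when the test statistic falls in the futility region".
- **Final look.** If neither boundary was crossed, the final z is compared with −1.9744, and a z below it rejects the null. The next branch, with a greater-than sign and no minus sign, reads "1.9744, we fail to reject the null hypothesis, claiming ETs do not reduce the malaria hazard rate compared to control".
- **After a crossing.** "If the interim results cross either the futility or efficacy boundaries, the final analysis is only conducted for estimation purposes". The reason given is that futility or efficacy has by then been established.

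**The concern.** This rule produces the trial's primary verdict, and the article states it with exact numbers, so it is not a detail left to the SAP. Two statements in it do not work.

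1. **Sign.** One branch ends at −1.9744 and the other starts at +1.9744, so the interval between them has no conclusion. The branch above +1.9744 cannot be saved as the upper limit of a two-sided test. A result there would reject in the direction of harm, as the interim rule recognises for its own upper limit.
2. **Futility.** A non-binding boundary leaves the final test available if the trial goes on. The text says the null need not be accepted after a crossing, then removes the only test that could reject it. For an efficacy crossing, estimation-only is coherent because the null has already been rejected. For a futility crossing it is a contradiction.

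If the trial crosses futility, continues and ends below −1.9744, one sentence supports a confirmatory claim and another forbids it. Settling that after the interim result is known would weaken the pre-specification.

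**Working it through.** **Inputs from the protocol.** The boundaries are set "with a 2-sided Type I error rate of 0.05, Type-II error rate of 0.2". Information at the interim is t = 0.5 (658 of 1315 events). The bounds are −2.7965 and −0.7288 at the interim and −1.9744 at the end. The design effect is protective efficacy (PE) 35%, from Sample size {14}.

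**Model.** Z₁ ~ N(−θ√0.5, 1), Z₂ ~ N(−θ, 1), correlation √0.5 = 0.7071.

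**The plan's own figures.** Classic two-look O'Brien-Fleming bounds at two-sided 0.05 are 2.7965 and 1.9774. The interim value reproduces exactly. The stated final value of 1.9744 does not; with it, two-sided alpha is 0.0503 instead of 0.0500. That difference is negligible and separate from this point. The stated 1.9744 is used below.

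**Drift θ (an assumption, since the document gives none).** For O'Brien-Fleming-shaped bounds, θ = (2.7965 − 0.7288)/0.7071 = 2.924. Solving for 80% power with futility enforced gives the same value.

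**Interim outcome**

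| | Null (θ = 0) | θ = 2.924 |
|---|---|---|
| Efficacy crossed | 0.0026 | 0.2331 |
| Neither crossed | 0.2305 | 0.6766 |
| Futility crossed | 0.7669 | 0.0903 |

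**Part 1, the sign.** The final rule applies only to trials that crossed neither boundary.

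| Final z, given neither crossed | Null | θ = 2.924 |
|---|---|---|
| Below −1.9744 | 0.0870 | 0.8379 |
| −1.9744 to +1.9744 (no verdict) | 0.9129 | 0.1621 |
| Above +1.9744 | 0.00006 | about 0 |

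As a share of all trials, the gap is 0.2305 × 0.9129 = 0.210 under the null and 0.6766 × 0.1621 = 0.110 at θ = 2.924.

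**Part 2, futility.** The probability of crossing futility and still ending below −1.9744 is 0.0025 under the null and 0.0305 at θ = 2.924.

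- One-sided alpha with the test removed: 0.0026 + 0.2305 × 0.0870 = 0.0226. With the test kept: 0.0226 + 0.0025 = 0.0252 after rounding (0.02264 + 0.00253 = 0.02517).
- Power with the test removed: 0.2331 + 0.6766 × 0.8379 = 0.8000. With the test kept: 0.8000 + 0.0305 = 0.8305.

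**Range over the assumed drift**

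| θ | Cross futility | Cross and still end below −1.9744 | Power, test removed / kept |
|---|---|---|---|
| 2.802 (fixed-sample drift for 80% power) | 10.5% | 3.2% | 76.6% / 79.8% |
| 2.924 (inferred) | 9.0% | 3.1% | 80.0% / 83.05% |
| 1.953 (PE 25%: 2.924 × ln 0.75 / ln 0.65) | 25.7% | 3.2% | 46.3% / 49.5% |

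The share of trials affected stays near 3% throughout.

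**The case against.** The strongest reply is that the sign is recoverable. The sentence before names a single threshold, −1.9744, so with rejection below it, non-rejection above it is the only coherent reading. That stands, and it makes the first part a probable slip. It still needs correcting. The other negative bounds in the same paragraphs keep their minus signs, so loss in text conversion is not an evident explanation.

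On futility, the reply is that the rule is conservative. Type I error falls, and power with futility enforced equals the planned 80% at the inferred drift. The hazard ratio and its interval would still be reported. All of this stands on size. It does not remove the contradiction between a boundary that need not lead to acceptance of the null and a final analysis with no test.

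Three stronger readings are tempting, and the document does not support them.

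- **About 95% of null results have no verdict.** That is P(|Z| < 1.9744) = 0.952 for a trial without an interim look. Here only 23.0% of null trials reach the rule, which gives 21.0% of all trials.
- **Harm would be misreported.** A trial reaching the rule already has an interim z below −0.7288. It then ends above +1.9744 in about 0.001% of all trials under the null. Harm at the interim has its own provision.
- **Type I error is inflated.** Removing a test can only lower it.

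The wording that non-rejection means claiming ETs do not reduce malaria is a loose gloss on a correctly named outcome. It can be tidied in the same edit.

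**Conclusion.** Both parts hold on the text. The sign leaves a literal gap, large among trials that reach the final test under the null (91%) and smaller at the inferred design effect (16%), but the adjacent sentence shows what was probably meant. The futility contradiction is the substantive defect. It costs about 3 percentage points of power (about 83% to 80%) and leaves disputed the status of a significant final result after a futility crossing. One-sided alpha is 0.0226 with the test removed and 0.0252 with it kept, so the cost is lost power and ambiguity, with no false-positive risk from removing the test.

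The power and crossing figures rest on a drift inferred from the boundaries and on a normal model with exactly 50% information at the interim. The textual contradictions rest on neither.

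**What to change.** Change the wording in the protocol, and in the SAP if it repeats the rule, before the interim look.

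1. State that if the final z ≥ −1.9744 the null is not rejected. Report this with PE and its 95% confidence interval, and do not claim that ETs have no effect.
2. Limit the estimation-only final analysis to a crossed efficacy boundary.
3. State that if futility is crossed and the trial continues, the final test at the final critical value remains confirmatory. The futility and final-analysis sentences then agree.

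Confirm the final critical value in the same edit (1.9744 as printed, or 1.9774 as the partner of 2.7965).

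The cost is a text amendment, with no change to sample size, data collection or the timing of the look. Timing matters because Interim analyses {21b} has the interim report go to the lead organization. A later choice about whether the final test counts could then be made with knowledge of the result.

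### The futility boundary is declared non-binding, yet a trial that crosses it and continues is denied the final hypothesis test

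*Protocol article*

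**What the plan says.** The Sample size section lists one interim analysis for efficacy and non-binding futility at 50% information. The Primary analysis section fixes the timing: "The interim analysis will occur when 658 events (50% information) are collected". With negative z favouring EaveTubes, the bounds are:

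- interim efficacy: z below -2.7965
- interim futility: z above -0.7288
- final critical value: -1.9744

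On crossing futility, the Primary analysis section says that the study may go on collecting data without inflating type I error, and that "the trial does not need to stop to accept the null hypothesis when the test statistic falls in the futility region at the interim stage".

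The next paragraph compares the final z with -1.9744 on condition that neither boundary was crossed at the interim. It ends: "If the interim results cross either the futility or efficacy boundaries, the final analysis is only conducted for estimation purposes". The reason given is that futility or efficacy has by then been established. No other section gives a final test to a trial that continued past futility. The section on additional analyses adds only a per-protocol analysis.

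**The concern.** A futility boundary is non-binding when a trial that crosses it and carries on may still reject the null at the end. The efficacy cut-offs are then computed as though the futility rule did not exist, which is why ignoring it costs no type I error. The closing paragraph withdraws that final test. For an efficacy crossing its reasoning is sound, because the null has already been rejected. For a futility crossing it contradicts the preceding paragraph, under which the null need not be accepted.

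If the interim result falls in the futility region and the trial continues, the second year of data cannot change the formal primary conclusion. A favourable 24-month result would also meet two conflicting prespecified rules, and choosing between them after the interim would look post hoc in a submission to the WHO advisory group.

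**Working it through.** **Inputs from the document**
- Error rates: "with a 2-sided Type I error rate of 0.05, Type-II error rate of 0.2".
- Effect: "True PE/Minimum effect size = 35" per cent, so rates of 1.5 and 1.5 × 0.65 = 0.975 per person-year.
- Variation: "baseline incidence rate of 1.5 per person-year, and between-cluster CV of 40" per cent, so k = 0.40.
- Size: "With 17 clusters per treatment, 55 children" per cluster, followed for 2 years.
- Attrition: "Loss to follow-up (LTFU) rate = 20" per cent.
- Interim at 658 of 1315 events, taken at the plan's stated 50% information.

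Signs are reversed below, so that positive z favours EaveTubes.

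**Model.** (Z1, Z2) is bivariate normal with correlation √0.5 = 0.7071 and means (0.7071θ, θ), where θ is the drift, the expected final z.

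**Step 1: the plan's boundaries.** The classic O'Brien-Fleming design at one-sided 0.025 with two equally spaced looks gives an interim bound of 2.7965, exactly as printed. With that interim bound, the final value is:
- 1.9774 if the futility rule is ignored (non-binding)
- about 1.925 if the futility rule at 0.7288 is enforced (binding)

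The printed 1.9744 is close to the first and well above the second. The cut-off is therefore essentially one that presumes the final test survives a futility crossing.

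**Step 2: drift under the design effect.** Two values bracket the range.
- Fixed-sample drift for 80% power: 1.96 + 0.84 = 2.80.
- Cluster-rate formula, assuming 55 × 2 × 0.8 = 88 person-years per cluster (how attrition enters is an assumption):
  - V = (1.5 + 0.975)/88 + 0.40² × (1.5² + 0.975²) = 0.0281 + 0.5121 = 0.5402
  - θ = (1.5 − 0.975) × √(17/0.5402) = 2.945

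**Step 3: what the cancelled test contains.** P(cross) = P(Z1 < 0.7288) and P(both) = P(Z1 < 0.7288 and Z2 > 1.9744). Power as written counts no rejection after a futility crossing. Power with the test kept assumes that the trial always continues.

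| θ | P(cross) | P(both) | Share of crossers | Power as written | Power, test kept |
|---|---|---|---|---|---|
| 2.80 | 10.5% | 3.2% | 30% | 76.5% | 79.7% |
| 2.945 | 8.8% | 3.0% | 34% | 80.5% | 83.6% |

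For a trial exactly at the futility bound, conditional power for the final test under the design effect is P(Z2 > 1.9744 given Z1 = 0.7288) = Φ(0.7288 + 0.7071θ − 1.9744/0.7071). This is 47% at θ = 2.80 and 51% at θ = 2.945, so a decision to continue would not be unreasonable.

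**Step 4: type I error (θ = 0, one-sided).**

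| Final value | Test cancelled after futility | Test kept |
|---|---|---|
| 1.9744 (printed) | 0.0226 | 0.0252 |
| 1.9774 | 0.0225 | 0.0250 |

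**The case against.** The strongest reply is that little goes wrong in practice. The rule as written is conservative: one-sided type I error is 0.0226, so no false claim becomes more likely. It matters only if the interim crosses futility and the trial then continues. The text permits stopping, and gives no probability that the committee would override. The final analysis would still produce a hazard ratio with a 95% confidence interval. All of this stands, and it limits how serious the point is.

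A reader might infer more than the document supports:

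- **That the stated 80% power is broken.** This depends on the drift. Power as written is 76.5% at 2.80 but 80.5% at the drift given by the plan's own rates, k and cluster numbers.
- **That 3 points of power are lost outright.** That is the maximum, reached only if the trial continues after every futility crossing.
- **That a continuing trial could show nothing.** It loses the confirmatory test, not the estimate. A trial between the two interim boundaries is tested as usual.
- **That the rule is simply a binding one.** A binding boundary requires stopping and would allow a lower final value, about 1.925. Here continuation is allowed and the cut-off is not lowered.
- **That restoring the test leaves type I error untouched.** It rises from 0.0226 to the design level.

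The reply does not remove the contradiction. The two adjoining paragraphs give different answers to whether the primary hypothesis can still be rejected after a futility crossing.

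**Conclusion.** The point holds as an internal contradiction in the primary decision rule. The boundary is called non-binding and the final critical value is essentially the non-binding one, but a trial that crosses futility and continues has no final test. Under the design effect, 9 to 11% of trials cross futility, and about a third of those would end beyond -1.9744. The cost is between 0 and about 3 points of power, depending on how often the trial continues after crossing.

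These figures rest on the stated 50% information, the printed boundaries and a drift of 2.80 to 2.945. If the interim look carried much more than half of the information, the loss would shrink towards zero. The rule neither inflates type I error nor removes the effect estimate. It should be fixed, and before the interim look, because a later choice between the two readings could be seen as driven by the data.

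**What to change.** Replace the last sentence of the Primary analysis section, and amend the condition that opens the same paragraph, so that together they say:

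- If the efficacy boundary is crossed, any later analysis is for estimation.
- If only the futility boundary is crossed and the trial continues, the final z is compared with the final efficacy critical value, as for a trial that crossed neither boundary, and that test decides the primary hypothesis.

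Check the final critical value in the same edit. With the test restored, one-sided type I error is 0.0250 at 1.9774 and 0.0252 at the printed 1.9744 (two-sided about 0.0503).

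The cost is a short wording change in the protocol, carried into the statistical analysis plan if it repeats the rule. Sample size and data collection do not change. One-sided type I error rises from 0.0226 to its design level of 0.025.
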